## Abstract

**Introduction:**

As mortality rates from COVID-19 disease fall, the high prevalence of long-term sequelae (Long COVID) is becoming increasingly widespread, challenging healthcare systems globally. Traditional pathways of care for Long Term Conditions (LTCs) have tended to be managed by disease-specific specialties, an approach that has been ineffective in delivering care for patients with multi-morbidity. The multi-system nature of Long COVID and its impact on physical and psychological health demands a more effective model of holistic, integrated care. The evolution of integrated care systems (ICSs) in the UK presents an important opportunity to explore areas of mutual benefit to LTC, multi-morbidity and Long COVID care. There may be benefits in comparing and contrasting ICPs for Long COVID with ICPs for other LTCs.

**Methods and analysis:**

This study aims to evaluate health services requirements for ICPs for Long COVID and their applicability to other LTCs including multi-morbidity and the overlap with medically not yet explained symptoms (MNYES). The study will follow a Delphi design and involve an expert panel of stakeholders including people with lived experience, as well as clinicians with expertise in Long COVID and other LTCs. Study processes will include expert panel and moderator panel meetings, surveys, and interviews. The Delphi process is part of the overall STIMULATE-ICP programme, aimed at improving integrated care for people with Long COVID.

**Ethics and dissemination:**

Ethical approval for this Delphi study has been obtained (Research Governance Board of the University of York) as have approvals for the other STIMULATE-ICP studies. Study outcomes are likely to inform policy for ICPs across LTCs. Results will be disseminated through scientific publication, conference presentation and communications with patients and stakeholders involved in care of other LTCs and Long COVID.

**Registration:**

Researchregistry: https://www.researchregistry.com/browse-the-registry#home/registrationdetails/6246bfeeeaaed6001f08dadc/.

## Introduction

Despite major reductions in acute COVID-19 hospitalisation and mortality [1], the persistence of symptoms over one year later is notable in the 45% of the 1.5 million individuals who had symptoms four weeks post-COVID in the UK [2–4]. Unlike some long-term conditions (LTCs), individuals with Long COVID (i.e. those with post-COVID symptoms >12 weeks) may still fully recover. However, new care pathways for Long COVID attempt to manage it akin to a LTC, given the increasing recognition of chronic symptoms [4, 5].

Care pathways for LTCs have tended to be disease- or specialty-specific, an approach which fails to accommodate the heterogeneity of symptoms occurring in Long COVID. ICPs are structured, multi-disciplinary plans of the whole care pathway from primary care to specialist services and rehabilitation services, which may be better suited to Long COVID [6–8]. They offer coordination of investigation, treatment and rehabilitation, as well as opportunities for real-time iterative improvements in service design and delivery, quality and access to care, patient experience and satisfaction, while reducing complications and non-elective admission rates [9–11]. Evolution of integrated care systems (ICSs) in the UK provide opportunities to improve care across LTCs, multi-morbidity or multiple health conditions [12], and Long COVID.

Long COVID encompasses a broad array of symptoms and symptom clusters. It is unlikely to reflect a single condition or pathology; rather it reflects a multi-faceted condition with numerous contributory factors: some identifiable, and others not yet understood [13]. Trajectory and recovery after SARS-CoV-2 infection are poorly defined and there is overlap with medically not yet explained symptoms (MNYES), referring to symptoms which do not represent a known medical condition, yet contribute significantly to lesser quality of life and treatment need [14]. Multi-organ complications [13, 15–18], including neuropsychiatric sequelae (up to 20%), are well-documented [19–24].

Table 1 shows current models that can potentially be applied to Long COVID ICPs. Depending on setting, expectations and provisions regarding treatment may differ. It can be argued that some current models for managing LTCs require improvement [25] as they cannot cover the whole range of patient presentations; episodic care is not appropriate for unpredictable exacerbating conditions, for example heart failure and COPD [26, 27]. An effort should be made to explore how to achieve integrated care from the perspective of individual conditions, but also from the perspective of how health services and settings can inform each other, and work together, to deliver optimal care for LTCs. The current pandemic and effort to set up Long COVID clinics [28] offers a unique opportunity to explore this from the perspective of Long COVID, and then to translate back to ICPs for other LTCs. For example, model 2 could also be based in primary care with better integration of GPs, primary care nurses and therapists. Model 3 could be more of a shared care arrangement between primary and secondary care with two-way data flow between these two sectors. In other words, one of the solutions for Long COVID care could be better working arrangements between community services, primary care and specialty care and ICSs might offer the perfect space for this in England.

**Table 1 pone.0277936.t001:** Potential models for ICPs managing recovery in Long COVID and other LTCs.

Model	Example condition(s)	Recovery time	Managed by	Approach
Model 1	Community Acquired Pneumonia (CAP)	This may take 6 months to fully recover in terms of fatigue (NICE guideline) [29]	Primary care teams and community General Practitioners (GPs). There is a NHS CAP CQUIN aiming to support discharge from the hospital and safe follow up of these patients.	Currently there is no well-developed integrated care pathway but there could be a chance to identify how to identify CAP follow up better based upon Long COVID care experiences.
				They support the patient through their recovery with the length of complete recovery and the ramifications for work often underestimated.
			Follow up imaging is usually arranged by secondary care.	
Model 2	Post myocardial infarction, significant musculoskeletal injury	Taking a medium course to resolution, e.g., 1–2 years.	Multi-disciplinary team (MDT) driven and mostly provided in rehabilitation clinics.	Rehabilitation approach, personalised to the individual including a biopsychosocial approach to care, with physiotherapy and medical attention to address anxiety and depressive symptoms
Model 3	A chronic disease like type 2 diabetes or stroke	It is managed but often recovery is not complete.	Usually managed in primary or community care, by GPs and diabetes nurses, or in the hospital setting.	Escalation of a small proportion with complex needs being managed in a specialist setting [30]
Model 4	COPD Rheumatoid Arthritis	A chronic condition that may have high disability with tendency for relapses/ exacerbations.	Limited care provision, mostly based in primary care with exacerbations increasingly managed in hospital in later stages. Growing emphasis on need to improve community diagnostics and where pulmonary rehabilitation is a key evidence-based treatment.	COPD is a condition that shares breathlessness as an important symptom with Long COVID, where pulmonary rehabilitation is a key evidence based treatment and supporting self-management is a key goal. Impact on function, breathlessness and psychological wellbeing as in Long COVID. Both conditions have a relapsing course of symptoms that may benefit from prompt intervention. There is growing emphasis on the need to improve community diagnostics.
Model 5	Comorbid mental disorders and other LTC.	These are in general chronic conditions with high disability.	Mental disorders have case management, crisis teams, psychiatry follow up, but they do not identify physical health needs of their patients, such as respiratory issues. And clinics for somatic conditions can have short-term treatments available for psychological treatments but there is a lack of available long-term integrated treatment.	There are pilot playgrounds for dedicated respiratory clinics for patients with mental illness across the country.
				Similar pilots exist for diabetes and depression—either community-based or hospital-based.
	For example, COPD in patients with mental disorders, often related to smoking.	There is an unmet clinical need here.		
	Or, depression in diabetes patients.			
Model 6	Encompassing multi-morbidity (i.e. more than two LTCs) as well as a spectrum of symptoms that do not fit into a usual pattern for diagnosis of a single disease i.e. MNYES [14], or both, crossing the mental health and physical health divide.	The perceived burden of disease is high.	No current consistent pathway of care exists. Consultation, collaborative care and decision aids supporting health care providers to provide ICP would be possibilities to link primary, community and specialist health care settings	These patients are highly likely to benefit from an ICP. This would be best served with a flag up system approach which is for people who don’t quite meet full diagnostic criteria in one condition but almost meet it in many conditions. This would be labelled as MNYES but disease burden is high and there is a need to integrate physical and psychological health care provision.
		These are conditions requiring a multisystem approach.		

Acronyms: Community Acquired Pneumonia (CAP), National Institute for Health and Care Excellence (NICE), General Practitioner (GP), National Health Service (NHS), Commissioning for Quality and Innovation (CQUIN), Multi-disciplinary team (MDT), Chronic Obstructive Pulmonary Disease (COPD), Long term condition (LTC), Integrated care pathway (ICP), Medically not yet explained symptoms (MNYES).

Even in well-defined entities such as community acquired pneumonia (CAP), symptoms such as fatigue [31] may take up to six months to resolve, even in young, physically fit people, fuelling fears that their symptoms will not abate, which may be biologically, psychologically, or socially driven, or depend on treatment setting. Learning from other LTCs, optimal Long COVID management may require a biopsychosocial model, rather than consideration of these components separately [32].

## Research question

What are effective ICPs for individuals with Long COVID and how can they be transferred to other LTCs including mental disorders, multi-morbidity and the interface between known medical disorders and MNYES [14] as well as newly developed conditions?

## Materials and methods

This Delphi study was reviewed and approved by the University of York Department of Health Sciences Research Governance Committee on 17^th^ December 2021 (HSRGC/2021/478/A:STIMULATE).

### Aims

In a Delphi study using a biopsychosocial approach, we will investigate:

(a) Key enabling elements for effective ICPs for individuals with long COVID, based on user experience, and (b) Strengths of existing ICPs for other LTCs.Which (part of an) ICP model for Long COVID can be transferred to other LTCs for which care pathways were not yet developed sufficiently, and how.Variations in uptake and adherence to treatment in Long COVID and LTCs.

### Study design and setting

This STIMULATE-ICP-DELPHI is a sub-study of the STIMULATE-ICP project (Symptoms, Trajectory, Inequalities and Management: Understanding Long COVID to Address and Transform Existing Integrated Care Pathways) [33]. (Fig 1).

**Fig 1 pone.0277936.g001:**
[figure not shown]
Flow chart showing the integration of STIMULATE-ICP DELPHI within overall STIMULATE-ICP.

STIMULATE-ICP is funded by the National Institute for Health Research (NIHR: COV-LT2-0043) [34] and combines clinical epidemiological studies, a complex randomised trial exploring the benefit of an ICP for Long COVID (IRAS: 1004698), and mixed methods studies exploring inequalities of care and transferability of the ICP to other LTCs (IRAS: 303958).

The STIMULATE-ICP-DELPHI study will follow a Delphi process to establish consensus agreement on statements relating to ICPs and the transferability of ICP models between Long COVID and LTCs. The Delphi approach is a structured method for collecting opinions of experts concerning a subject of their expertise, reaching consensus over a number of rounds [35]. Since its development in the 1950s [36] a commonly used variation of the Delphi method is the *estimate-talk-estimate Delphi method* that combines assembling of expert opinions on an anonymous basis during surveys with open exchange during workshops moderated by a facilitator [37]. This Delphi method will be followed in this study [38], aiming for stepwise consensus through three rounds of expert panel meetings involving exploration, prioritization, and as a final step attaining consensus (Fig 2).

**Fig 2 pone.0277936.g002:**
[figure not shown]
Outline of Delphi process.

The meetings will be interwoven by two online surveys, with addition of qualitative interviews. After a “knowledge check”, an information package based on the survey and interview outcomes will be provided to the panel. The expert panel will then discuss outcomes and provide policy recommendations in a final meeting [39].

This study will depart from the theoretical framework of Goldberg and Huxley’s filter-model of access to care [40, 41] that describes four filters; three of which a patient has to navigate to enter a primary care treatment pathway, and a fourth to access specialist treatment. This model was originally developed for access to care for mental disorders, but it would be a good fit for exploring barriers and facilitators to entering Long COVID services and other LTCs not only for psychological symptoms but for physical symptoms as well. This extended model spans multiple healthcare challenges and extends the existing inequalities in health such as limited access to healthcare, incomplete pathways across community and hospital care, inadequate research translation to practice, and overall insufficient healthcare resources (Fig 3).

**Fig 3 pone.0277936.g003:**
[figure not shown]
Filter model, expanded to conceptualise access to care for Long COVID or other long-term conditions (LTCs) including medically not yet explained symptoms (MNYES) and multi-morbidity.

People with Long COVID and those with LTCs frequently present to healthcare services with multiple symptoms [42–44]. Therefore, this study will take account of competing demands to determine how people seeking support prioritise their symptoms when seeking help, and how healthcare providers deal with multiple symptoms reported when making decisions about appropriate care [45, 46].

## Study management

This work will involve a research team (n = 3), a moderator panel (MP) (n = 3) and an expert panel (EP)(n = 25). The research team will prepare, distribute and analyse all information for the project. The MP will meet regularly, providing advice and guidance to the research team to ensure scientific quality. The EP will include people with expertise in academic and clinical research in addition to lived experience of Long COVID, other LTCs such as cardiovascular disorders, type 2 diabetes, mental disorders and MNYES, or multi-morbidity; 5 of each group with a minimum of 25.

EP members will be selected by the MP building on suggestions from the Royal College of General Practitioners and national charities following a snowballing method. Patients with illness experience of Long COVID and other LTCs will be identified by clinics, medical trusts, patient networks and charities following a snowballing method. As part of the invitation process, the research team will inform prospective EP members about their role within the study. The EP will provide information and advice relating to their experiences of living with, or supporting people with Long COVID or LTCs.

### Sample size, participant characteristics, inclusion and exclusion criteria

Recruitment for Survey 1 will involve collecting quantitative and qualitative data from two purposive samples selected from community, primary care, and specialist settings. Sampling will seek to achieve sufficient numbers (minimum of N = 50 per group) in order to have a representative sample. Sample 1: patients/carers and clinicians with experience of Long COVID and other post COVID morbidity across England. Sample 2: patients/carers and clinicians involved in other LTCs. Participants in both samples will be recruited via the study website, with support from relevant online forums, associations and charities. As personalised care is now a specific NHS workstream which is intended to touch on all the LTC pathways, we will seek the opinion of ICS stakeholders (commissioners and those involved in the clinical networks) as to how personalised care should be delivered [47–52].

The selection of interviewees for the qualitative study will be nested in the surveys. Participants from Survey 1, willing and able to provide informed consent, will be invited (using a separate survey link) to express interest in participating in an interview to discuss their experiences of healthcare relating to Long COVID and/or LTCs. Using details from the expression of interest form, the research team will select a purposive sample of people (minimum N = 10–15) to interview. Within those volunteers, a maximum variation approach to participant selection will be adopted to ensure a wide range of experiences are reflected (accounting for experience of Long COVID and/or LTC(s), patient/clinician). Sampling will stop once saturation is reached. Both patients and clinicians will be interviewed as to how they deal with multi-morbidity or multiple symptoms and competing demands when accessing or providing healthcare, and the barriers and facilitators to providing or receiving ICP [53–60].

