### Study processes

#### Round 1

During the initial EP meeting, the scope of this work will be agreed. This work will focus on adults (18 and over); outcomes will include confirming the list of relevant LTCs and those considered out of scope. As an inclusive approach, a variety of LTCs including mental disorders, multi-morbidity and the interface with MNYES will be considered. Fatigue, as a symptom, will be in scope, myalgic encephalomyelitis or chronic fatigue syndrome (ME/CFS) will be considered out of scope for this survey. Cognitive limitations will be in scope, non-capacity will be out of scope for the survey. Following confirmation of the scope, EP members will discuss and agree on questions to ask in Survey 1. The survey will include questions about:

1) Demographic factors (age, gender, ethnicity), relevant disease experience as patient or clinician, and clinical and work functioning profile of participants.

2) Experiences of Long COVID which prompted help-seeking with a focus on the process of seeking treatment, referrals, treatment(s) offered and received and whether there were any barriers or facilitators to that.

3) Challenges and advances for clinical care, knowledge gaps and policies, possible improvements to services, transferability of care models to other conditions will be explored for Long COVID and for other LTC ICPs.

#### Survey 1

This will be an anonymous, online survey (using the Qualtrics [61] platform) to establish demographic information and to explore the topics by open questions. Participants will also be invited to give a first indication of what their priorities to improve integrated care would be.

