### Data analysis and outcomes

Data analysis will provide descriptive statistics to outline the demographic characteristics of the two samples. Item response frequencies provide information about the current services offered. Open-ended questions will capture individual experiences of services and suggestions for future improvements. Responses will be organised into themes, with the research team adopting a pragmatic approach to provide feedback for the second expert panel meeting.

Thematic analysis will be conducted on data transcripts for round 1 interviews [65]. Theme development will be derived deductively from the topic guide. However, we will also allow for inductive theme development and will actively seek to identify new themes or topics within our data [66]. Following initial deductive and inductive coding, analysis will be set in the context of relevant theoretical concepts from the experience of chronic illness, such as, for example, the adapted Goldberg and Huxley’s filter model [40]; competing demands in primary care [46]; biographical disruption [67]; and illness careers [68]. Emergent patterns and early analysis will be discussed at regular research and moderator panel meetings for comment. Data from Survey 1 and Interviews will be combined and presented to the EP for consideration during round 2 of this study.

Data analysis will collate responses to Survey 2. Then consensus of opinion about each statement will be assessed using interquartile deviations (IQD). For this calculation, at least 50% of individuals will have responded using the same category. IQD ≤ 1 is considered to indicate consensus. Findings from survey 2 will be combined with an information pack based upon input from other STIMULATE-ICP sub studies as lined out in Fig 1, and shared with the EP members.

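### A minimum of 50 per group cannot make purposive, openly recruited online samples representative, and *group* is undefined although each sample pools patients/carers with clinicians

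*Protocol article*

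**What the plan says.** All of the following is in the Protocol article. The section on sample size, participant characteristics and eligibility describes Survey 1 as drawing on "two purposive samples selected from community, primary care, and specialist settings". The next sentence gives the size and its purpose: "Sampling will seek to achieve sufficient numbers (minimum of N = 50 per group) in order to have a representative sample". The two samples are then defined, the first in these words: "Sample 1: patients/carers and clinicians with experience of Long COVID and other post COVID morbidity across England". The definition of the second has the same form and again joins the two roles: "Sample 2: patients/carers and clinicians involved in other LTCs". Both have the same recruitment route: "Participants in both samples will be recruited via the study website, with support from relevant online forums, associations and charities".

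Under Study processes, Survey 1 is introduced thus: "This will be an anonymous, online survey (using the Qualtrics [61] platform) to establish demographic information and to explore the topics by open questions". The question list in that section includes age, gender, ethnicity and whether the respondent's disease experience is as patient or clinician.

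Under Data analysis and outcomes: "Data analysis will provide descriptive statistics to outline the demographic characteristics of the two samples". The same paragraph says that item response frequencies will inform about the services now on offer, and that open responses will be organised into themes for the second expert panel meeting.

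**The concern.** Two things look wrong.

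First, representativeness comes from how respondents enter the sample, not from how many there are. A purposive sample is a non-probability sample. Open recruitment through a website, forums and charities means that respondents largely choose themselves; the article does not use that term, but it is a fair inference from the route. The sentence that justifies 50 therefore promises something the design cannot deliver, one sentence after naming the design that prevents it.

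Second, the minimum is set per group, without saying whether a group is one of the two samples or a role within a sample. Each sample contains both roles. If group means sample, nothing in the article stops 50 being reached almost entirely with patients/carers or almost entirely with clinicians.

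At stake is what the Survey 1 frequencies can be taken to show. Labelled representative, they invite a reading as estimates for people with Long COVID or other long-term conditions, or for their clinicians. Pooled over roles, they may also reflect who happened to answer more than what either role reports.

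**Working it through.** **1. Can N = 50 be reproduced?** No. The article states no target precision, target population, sampling frame or weighting, and no hypothesis test from which a size could be derived. A purposive Delphi survey needs no power calculation, so this is not an arithmetic error. It does mean that nothing beyond the count supports the word *representative*.

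**2. Does the count help against selection?** The inputs here are assumptions. Let p be the true proportion holding a view, and let those who hold it be r times as likely to respond. The expected sample proportion is r·p / (r·p + 1 − p). With p = 0.50:

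| r | calculation | expected in sample |
|---|---|---|
| 1.0 | 0.50 / (0.50 + 0.50) | 50% |
| 1.5 | 0.75 / (0.75 + 0.50) | 60% |
| 2.0 | 1.00 / (1.00 + 0.50) | 67% |
| 3.0 | 1.50 / (1.50 + 0.50) | 75% |

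N does not appear in the formula. The shift is the same at 50 as at 500.

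**3. What does *group* mean?**

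- Group = sample: 2 × 50 = at least 100 respondents, with no floor by role.
- Group = role within sample: 4 × 50 = at least 200 respondents, and 50 is itself the floor for each role.

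The sentence directly follows the mention of two samples, so the first reading is the more natural. The second is possible: the Data saturation section uses the word for interview participants with a parenthesis that can be read as role by condition. The text does not settle it. Composition is handled elsewhere in the plan: the Study management section asks for five of each expert-panel group, and interviewees are selected "accounting for experience of Long COVID and/or LTC(s), patient/clinician".

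**4. What does the role mix do to a pooled frequency?** This applies on the first reading, again with assumed inputs. Let w be the patient/carer share. The pooled proportion is w·p₁ + (1 − w)·p₂. With p₁ = 0.70 (patients/carers) and p₂ = 0.30 (clinicians), and 50 respondents:

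| w | patients/carers : clinicians | calculation | pooled |
|---|---|---|---|
| 0.9 | 45 : 5 | 0.63 + 0.03 | 66% |
| 0.5 | 25 : 25 | 0.35 + 0.15 | 50% |
| 0.1 | 5 : 45 | 0.07 + 0.27 | 34% |

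All three meet the minimum. In general the range equals the change in w times the gap between roles. For w from 0.1 to 0.9 that is 0.8 × 0.40 = 32 points. With a gap of 20 points it is 0.8 × 0.20 = 16, with a gap of 10 it is 8, and with no gap it is 0. The article gives no figure for the gap.

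**The case against.** The strongest reply is that this is a Delphi study. Purposive sampling is legitimate in it, and for generating statements a range of experience matters more than prevalence. Survey 1 is exploratory. Recommendations come only after interviews, panel-written statements, Survey 2 ratings, an information pack and a final panel meeting. A journal article may also leave quotas to the full protocol, and a sampling frame or response rate is not to be expected for open purposive recruitment. All of this stands. It limits the severity and confines the criticism to the claim made, not to the method chosen. It does not rescue the sentence, which states a property the design lacks.

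Four stronger readings are tempting and are not supported.

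- A reader might infer that the plan certainly sets no floor by role. Because *group* is undefined, that is likely but not certain.
- A reader might measure the defect by the margin at n = 50, 1.96·√(0.25/50) = ±13.9 points, or at n = 25, 1.96·√(0.25/25) = ±19.6 points. These are precision under simple random sampling, which does not apply here. They do not measure representativeness, and 50 is a minimum, not the expected size.
- A reader might link the under-served group mentioned in Table 2 to people without online access. Table 2 uses that description for long-term conditions, not for digitally excluded people.
- A reader might infer that Survey 1 frequencies go straight into policy as population estimates. No section says so.

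**Conclusion.** The concern holds in limited form. It is certain from the text that the article offers a count as the route to a representative sample while describing purposive, openly recruited samples, and that is wrong as written. It is also certain that each sample pools roles and that *group* is not defined. That 50 can be met with very few of one role follows only if group means sample, the more natural but not the only reading.

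The size cannot be taken from the documents. The illustrations show that selection shifts do not shrink with N, and that a pooled frequency could move by 0 to 32 points between mixes of 90:10 and 10:90 for role gaps of 0 to 40 points. The severity is modest: the change corrects what Survey 1 can be said to show and does not call the Delphi process into question.

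**What to change.** 1. Replace the representativeness claim with wording such as: a purposive sample covering a range of experience; frequencies describe respondents only.
2. Define *group*. If it means the pooled sample, state a minimum for patients/carers and for clinicians within the existing total. The documents give no basis for a particular split, so the study team should choose and justify it.
3. Report Survey 1 item frequencies separately for patients/carers and clinicians, within each sample. Role is already among the planned questions. Carers are not named in that item as the article describes it, so check that they can be identified.

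Do not attach 95% intervals to these frequencies. On self-selected data they would invite the population inference that the rewording is meant to remove.

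The cost is a less favourable claim, one definition and a few more table columns, with no increase in the total. The timeline has Survey 1 open from April to June 2022. If it has closed, a minimum by role can no longer steer recruitment, but the rewording, the definition and the tabulation by role still apply.
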